# **4 STATISTICS AND METHODOLOGY**

## **4.1. Statistical analysis plan and sample size calculation**

### *Sample Size calculation*

Sample size was estimated to provide sufficient power to detect a clinically meaningful difference of 10% in the primary efficacy outcome. The sample size was calculated based on preliminary data on the efficacy of SNAQ app in improving postprandial glucose control. In data from 23 subjects (1603 meals with SNAQ app and 2018 meals without SNAQ app), mean $\pm$ SD time in target range was 85 $\pm$ 23% vs. 77 $\pm$ 35% with and without the app, respectively. Assuming a mean improvement of 10% in the intervention group with no change in the control group, and assuming

a within-participant standard deviation of 10% in both groups, a total sample size of 34 participants (17 per group) is required to achieve a power of 80% at a two-sided alpha level of 5%. Assuming a drop-out rate of 20%, we therefore aim to recruit 44 participants (22 per group).

#### *Statistical analysis*

For the efficacy analysis, outcomes will be compared between the two groups using general linear models (GLM). All endpoints evaluating the efficacy of the intervention (main analysis) will be adjusted for their values at baseline. For the sustainability analysis, baseline data and the 3 weeks following SNAQ app discontinuation will be compared using pooled data from both groups. GLM techniques considering the paired data structure will be used. In case of non-normality of the residuals, data will be transformed appropriately. All analyses will be performed using all available data (see section 4.2 for handling of missing data). P-values below 5% will be considered statistically significant. Exploratory endpoints will be reported as point estimates with 95% confidence intervals (unadjusted for multiple testing), so definite inferences cannot be made regarding those endpoints.

Statistical analysis will be performed using the software R and/or Stata. A detailed statistical analysis plan will be written before the start of the study.

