- 11) Change in the percentage of time with postprandial sensor glucose in hyperglycaemia ( $>10.0\text{mmol/L}$ , %).
- 12) Change in the percentage of postprandial time with sensor glucose in hypoglycaemia ( $<3.9\text{mmol/L}$ , %).

Note: For all outcomes evaluating sustainability of the improvements, glucose control endpoints calculated at baseline and in the 3 weeks period of SNAQ use will be compared with the variables calculated during the 3 weeks following discontinuation of the app. Baseline glucose control endpoints will be calculated over the 14 days prior to randomization (day -14 to day -1). Glucose control endpoints during the 3 weeks following discontinued use of the SNAQ app will be calculated as follow: Visit 2 + 1 Day to Visit 2 + 21 Days for the intervention group and Visit 3 + 1 Day to Visit 3 + 21 Days for the control group. Postprandial periods are defined as above.

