## **3.5 Randomization**

Eligible participants will be randomly allocated (1:1) to the intervention group or the control group. Group allocation will be done according to an adaptive stratified randomization framework using the minimization method, implemented in the MinimPy randomisation software to balance between group characteristics. The following minimisation factors will be considered: glycated haemoglobin A1C ( $<7.5$  or  $\geq 7.5$  %), sex, time in target range (3.9-10.0mmol/L) in the 14 days prior to the study inclusion ( $>75\%$  or  $<75\%$ ).

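### Allocation is minimised on HbA1c, sex and baseline time in range, but the efficacy model names only the endpoint's own baseline value; if HbA1c or sex is prognostic beyond that, precision is forgone

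*Protocol*

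**What the plan says.** Protocol section 3.5 describes the allocation as an "adaptive stratified randomization framework using the minimization method, implemented in the MinimPy randomisation software to balance between group characteristics". The factors are HbA1c (cut at 7.5%), sex, and "time in target range (3.9-10.0mmol/L) in the 14 days prior to the study inclusion" (cut at 75%).

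Protocol section 4.1, under the statistical analysis heading, compares the groups with general linear models and gives one adjustment rule: "All endpoints evaluating the efficacy of the intervention (main analysis) will be adjusted for their values at baseline". HbA1c and sex are not mentioned there. The same section says that a detailed statistical analysis plan will be written before the study starts; that plan is not at hand.

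For the primary endpoint, the baseline covariate is time in range over the 14 days before randomisation. This is the continuous form of the third minimisation factor, so that factor is covered. HbA1c and sex are not. For the other efficacy endpoints, baseline time in range is not named either.

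**The concern.** Minimisation makes the groups more alike on the chosen factors than simple randomisation would. If a factor predicts the outcome, its contribution is largely removed from the treatment contrast. If the analysis model omits that factor, its variance still sits in the residual. The reported standard error is then larger than the true sampling variability of the estimate, and the test rejects too rarely under the null.

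What is at stake is efficiency, and agreement between design and analysis, in a trial that needs 34 evaluable participants. Both factors are known before randomisation: HbA1c is an eligibility criterion, and both are inputs to the allocation.

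**Working it through.** **Inputs from protocol section 4.1.** Difference 10 percentage points, SD 10, two-sided alpha 5%, power 80%, 34 participants (17 per group), 20% drop-out, 44 recruited (22 per group).

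**Reproducing the plan's figure.** The two-sample t test (noncentral t) has power 78.1% at 16 per arm and 80.7% at 17, so 17 per arm is right. For drop-out, 17 / 0.8 = 21.25, rounded up to 22 per arm, or 44. Neither figure relies on adjusting for HbA1c or sex.

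**Assumptions.** R² is the share of the variance left after baseline adjustment that HbA1c class and sex explain. The protocol gives no value, so a range is used. SD 10 is taken as the residual SD after baseline adjustment. The protocol calls it a within-participant SD and does not say which residual it stands for.

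**Power with and without the factors.** The standard error is SD × √(1 − R²) × √(2/n), and the noncentrality is 10 divided by it. Degrees of freedom are 2n − 3 for the baseline-only model and 2n − 5 with two more terms. At n = 17, the baseline-only model has standard error 10 × √(2/17) = 3.43, noncentrality 2.92 and power 80.6%.

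| R² | SE with factors (17 per arm) | Noncentrality | Power, 17 per arm | Power, 22 per arm |
|---|---|---|---|---|
| 0 | 3.43 | 2.92 | 80.4% | 89.9% |
| 0.05 | 3.34 | 2.99 | 82.4% | 91.3% |
| 0.10 | 3.25 | 3.07 | 84.4% | 92.6% |
| 0.20 | 3.07 | 3.26 | 88.3% | 95.1% |

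The baseline-only comparators are 80.6% at 17 per arm and 89.9% at 22 per arm.

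**Simulation check.** Minimisation on the three factors was simulated with 34 participants and 4,000 runs per setting. A biased coin of 0.8 and a correlation of −0.7 between baseline time in range and HbA1c were assumed; neither is in the protocol.

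| R² | Baseline-only: model SE vs true SD (null) | Baseline-only type I error | Power, baseline only vs with factors |
|---|---|---|---|
| 0 | 3.43 vs 3.38 | 4.4% | 80.0% vs 79.0% |
| 0.05 | 3.42 vs 3.36 | 4.4% | 79.4% vs 79.7% |
| 0.10 | 3.44 vs 3.38 | 4.5% | 80.9% vs 82.7% |
| 0.20 | 3.44 vs 3.29 | 3.8% | 80.7% vs 86.9% |

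The Monte Carlo standard error of a 5% rejection rate is √(0.05 × 0.95 / 4000) = 0.34 points. The rates of 4.4% to 4.5% are therefore within about two standard errors of 5%. At R² = 0 the omitted factors cannot be the cause. Conservatism is clear only at 0.20, where 3.8% lies more than three standard errors below 5%.

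**Secondary endpoints.** By the protocol's definitions, time in range, time above 10.0 and time below 3.9 mmol/L sum to 100%. Baseline hyperglycaemia is thus 100 minus time in range minus hypoglycaemia, and adjusting for it already carries most of the time-in-range factor. The omission is more relevant for the hypoglycaemia endpoints. These were not simulated.

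**The case against.** Three objections have force.

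- **The rule is not exclusive.** A reader might infer that the model contains the baseline value and nothing else. Section 4.1 does not say so, and the deferred analysis plan may add covariates. This stands, and it rules out calling the sentence an error. It does not remove the point: the protocol states an adjustment rule for all efficacy endpoints, and that rule can be brought into line with section 3.5.

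- **The loss is conditional.** A reader might infer that standard errors are certainly too wide and power certainly lost. That requires HbA1c or sex to predict three-week time in range beyond continuous baseline time in range, and the protocol gives no figure for this. HbA1c and 14-day time in range both reflect prior glucose control, so the added information may be small (an assumption). At R² = 0 the extra terms cost a little power.

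- **Planned power is not undermined.** A reader might infer a drop well below 80%, for example 71% against 79% when each factor shifts the outcome by 8 points. That arises from adding the factors' variance on top of the planned SD. With two evenly split, independent factors (assumed), each adds 0.25 × 64 = 16, so the baseline-only SD becomes √(100 + 32) = 11.5. The factors' share is 32/132, about 24%, which nothing in the protocol supports. If SD 10 is the baseline-adjusted residual, simulated baseline-only power stays at about 79% to 81% over the R² range tabulated.

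Nor does the baseline-only analysis inflate type I error, so a positive result from it would not be in doubt.

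**Conclusion.** This is a minor but real point about efficiency and about matching the analysis to the allocation. The stated model omits two factors on which allocation is balanced for the primary endpoint, and a third by name for the other efficacy endpoints. Omitting a prognostic balancing factor makes the test conservative.

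The size is unknown because the protocol does not give the R². By the formula, the gain at 17 per arm is about 2 points of power at R² 0.05, 4 at 0.10 and 8 at 0.20. The simulated gains are smaller: 0.3, 1.8 and 6.2 points. The effect is negligible up to about 0.05, small at 0.10 and material from about 0.20. These figures rest on SD 10 being the baseline-adjusted residual SD and, for the simulation, on the assumed coin and correlation. The sample size of 34 (44 recruited) stands.

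**What to change.** In protocol section 4.1, state that the efficacy model includes treatment group, the baseline value of the endpoint, and the minimisation factors HbA1c and sex, plus baseline time in range where it is not already the baseline value. State whether HbA1c enters as the 7.5% class or as a continuous covariate. If the analysis plan already lists these terms, align the protocol sentence with it.

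The cost is one sentence and two or three degrees of freedom, with no new data. If the factors are not prognostic, the loss is at most about 1 point of power (80.6% to 80.4% by formula, 80.0% to 79.0% simulated). The sample size need not change.

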#### **Secondary endpoints:**

*The following endpoints will be assessed to evaluate the effect on glucose control:*

- 2) Percentage of time with sensor glucose in hyperglycaemia (>10.0mmol/L, %)

Note: Time in hyperglycaemia during the intervention period will be calculated over the 3-week intervention period (Day 1 to Day 21).

- 3) Percentage of time with sensor glucose in hypoglycaemia (<3.9mmol/L, %)

Note: Time in hyperglycaemia during the intervention period will be calculated over the 3-week intervention period (Day 1 to Day 21).

*The following endpoints will be assessed to evaluate the effect on postprandial glucose control:*

- 4) Percentage of postprandial time with sensor glucose in target range (3.9 to 10.0mmol/L, %).

Note: Time in target range during the intervention period will be calculated over the 3-week intervention period (Day 1 to Day 21). Postprandial periods are defined as the 180 min following main meal intake. Main meals are defined as CHO amounts above 25g entered by the participants in the hybrid closed-loop system.

- 5) Percentage of postprandial time with sensor glucose in hyperglycaemia ( $>10.0\text{mmol/L}$ , %).

Note: Time in hyperglycaemia during the intervention period will be calculated over the 3-week intervention period (Day 1 to Day 21). Postprandial periods are defined as the 180 min following main meal intake. Main meals are defined as CHO amounts above 25g entered by the participants in the closed-loop system.

- 6) Percentage of postprandial time with sensor glucose in hypoglycaemia ( $<3.9\text{mmol/L}$ , %).

Note: Time in hypoglycaemia during the intervention period will be calculated over the 3-week intervention period (Day 1 to Day 21). Postprandial periods are defined as the 180 min following main meal intake. Main meals are defined as CHO amounts above 25g entered by the participants in the hybrid closed-loop system.

*The following endpoints will be assessed to evaluate the sustainability of potential improvements:*

- 7) Change in the percentage of time with sensor glucose in target range ( $3.9$  to  $10.0\text{mmol/L}$ , %)
- 8) Change in the percentage of time with sensor glucose in hyperglycaemia ( $>10.0\text{mmol/L}$ , %)
- 9) Change in the percentage of time with sensor glucose in hypoglycaemia ( $<3.9\text{mmol/L}$ , %)
- 10) Change in the percentage of time with postprandial sensor glucose in target range ( $3.9$  to  $10.0\text{mmol/L}$ , %).

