## **2.2 Study design**

### *Main study*

The study will follow a randomized two-arm parallel design. Study visits will be done remotely via video calls or in-clinic when coinciding with usual care appointments. Following a baseline visit and before randomization, baseline characteristics and medical history of the participants will be collected (as detailed in section 4.3). Following randomization, the intervention group will use SNAQ app for the first 3 weeks while the control group will proceed without any modification/intervention by the study team. After the first 3 weeks, the control group will undergo 3 weeks of SNAQ app use (weeks 4-6). At the end of their respective SNAQ app periods (weeks 4-6 for the intervention group and weeks 7-9 for the control group), both groups will discontinue the use of SNAQ app for 3 weeks to assess sustainability of potential effects. Finally, both groups will be offered to use SNAQ app for 3 additional weeks as per their preference (follow-up period). The study design is illustrated in **Figure 1**.

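### The sustainability analysis (secondary endpoints 7–12) is a pooled before–after comparison without a control, so any change common to all participants since enrolment would count as a retained app effect

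*Protocol*

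**What the plan says.** Protocol section 4.1 treats the two questions differently. Efficacy is compared between the randomised groups, adjusted for baseline. For sustainability, "baseline data and the 3 weeks following SNAQ app discontinuation will be compared using pooled data from both groups", and "GLM techniques considering the paired data structure will be used". No control, group or period term is mentioned.

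Section 2.1 lists endpoints 7–12 as secondary: "The following endpoints will be assessed to evaluate the sustainability of potential improvements". Its note sets baseline as the 14 days before randomisation and names two comparators for the post-app weeks: "glucose control endpoints calculated at baseline and in the 3 weeks period of SNAQ use will be compared" with them. Section 4.1 mentions only the first.

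Section 4.1 calls p-values below 5% significant. Its warning against definite inference covers exploratory endpoints only, so endpoints 7–12 are open to a significance claim.

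By section 2.2, the intervention group uses the app in weeks 1–3 and is off it in weeks 4–6. The control group has no app in weeks 1–3, uses it in weeks 4–6 and is off it in weeks 7–9.

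**The concern.** A paired change from baseline, pooled over everyone, cannot separate what the app left behind from whatever else changed after enrolment. The test is valid for whether time in range changed, but not for whether an app-induced improvement lasted, which is the stated objective.

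The protocol itself makes some common change plausible. Baseline precedes randomisation, while the post-app weeks lie several weeks into the study. Section 3.3 asks for stable diabetes therapy only where possible and gives confounding as the reason. Both groups answer a meal-management questionnaire at baseline and a nutrition-literacy questionnaire at baseline and Visit 1, which may direct attention to carbohydrate counting with or without the app.

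The control group's weeks 1–3 measure change without the app over the same follow-up, yet the sustainability analysis does not use them. At stake is a significant result being reported as a lasting benefit when it may be drift, or a real lasting benefit being cancelled by drift in the other direction.

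**Working it through.** **Inputs from section 4.1.** Difference 10 points; SD 10 points, described as within-participant; 17 per group (34); 80% power; two-sided 5%; 20% drop-out; 44 recruited.

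**The plan's own figure.** Normal approximation: n per group = 2 × (1.960 + 0.842)² × 10² / 10² = 15.7, so 16. With the noncentral t, 16 per group gives 78.1% power and 17 gives 80.7%. Then 17 / 0.8 = 21.25, so 22 per group and 44 in all. The stated sample size reproduces. The protocol gives no figure for the sustainability analysis.

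**Inputs assumed here.** True lasting effect S; common drift d from baseline to the post-app weeks; SD of change 10 or 14.1. The second value applies if 10 is the SD of a single period and periods are uncorrelated: 10 × √2 = 14.1.

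**What the pooled test estimates.** The expected pooled change is S + d. Its standard error is SD/√N: 10/√34 = 1.71, 14.1/√34 = 2.43, 10/√44 = 1.51. Set S = 0. The rejection rate follows from the noncentral t with N − 1 degrees of freedom and noncentrality d/SE; for d = 3, N = 34 and SD 10 this is 3/1.71 = 1.75.

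| Drift d (points) | N=34, SD 10 | N=34, SD 14.1 | N=44, SD 10 | N=44, SD 14.1 |
|---|---|---|---|---|
| 0 | 5% | 5% | 5% | 5% |
| 2 | 20.5% | 12.6% | 25.4% | 15.1% |
| 3 | 39.7% | 22.5% | 49.4% | 28.0% |
| 5 | 80.8% | 51.7% | 90.0% | 63.0% |

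The N = 44 columns assume no drop-out. Simulation at N = 34 and SD 10 agrees (20.8%, 39.6% and 80.4%).

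**Downward drift.** With S = 5 and d = −3 the expected change is 5 − 3 = 2 points. Power falls from 80.8% to 20.5% (N = 34, SD 10).

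**Intervention weeks 4–6 against control weeks 1–3, both baseline-adjusted.** Under a constant drift, the expectation is (S + d) − d = S, and the simulated rejection rate with S = 0 stays near 5% at every d tried. SE = 10 × √(2/17) = 3.43. Power at 17 per group is 80.7% for a 10-point and 29.3% for a 5-point lasting effect. Drift between the two windows remains: if it grows by 1, 2 and 3 points over the three periods, this contrast is biased by 2 − 1 = 1 point and rejects in 5.9% of trials, while the pooled change is biased by (2 + 3)/2 = 2.5 points and rejects in 29.3%.

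**Concurrent contrast in weeks 4–6.** With app effect A, intervention (off) minus control (on) is S − A. That is the effect of stopping. It is zero under full retention and also if the app never worked.

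**Sum of both concurrent contrasts.** A + (S − A) = S, whatever the common drift, provided A is the same in both periods. The SD per participant is 10 × √(2(1 + ρ)), with ρ the correlation between periods, so SE = 4.85 at ρ = 0 and 6.32 at ρ = 0.7. Power for a 10-point lasting effect is 52% to 34%.

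**Windows.** The note in section 2.1 starts the post-app windows the day after Visit 2 (intervention) and Visit 3 (control). Section 2.2 and the Visit 1 and Visit 2 text in section 3.3 stop the app at Visits 1 and 2. Read literally, the note's windows fall in the free-access period after each group's last visit. For the control group, Appendix 1 plans only an app-data download at the end of that period.

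**The case against.** The pooled change is simple, uses both groups and has half the standard error of the controlled contrast. No drift is documented, and the sample-size paragraph assumes no change in the control group. Therapy is to be kept stable where possible, and settings are recorded for each period. Control weeks 1–3 are the comparator in the efficacy analysis, so a large drift would be visible there. Sustainability is only a further objective.

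Much of this stands. The drift size is an assumption, and the primary conclusion is untouched. But precision does not help when the quantity estimated is effect plus drift, and nothing in the plan carries the control group's weeks 1–3 into the sustainability result.

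Three stronger readings are tempting and are not supported:

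- A reader might infer that the trial already holds a concurrent randomised comparison of after-app with never-app. It does not: the control group is on the app from week 4. The concurrent contrast measures loss on stopping, and the retention contrast spans different calendar weeks.
- A reader might infer that a mixed model with app state and period gives the same answer as comparing intervention weeks 4–6 with control weeks 1–3. It does not: the never state occurs only in period 1, so the model estimates retention as the sum of the two period contrasts, with its extra assumption and larger standard error.
- A reader might infer that section 4.1 abandons the on-app comparison. It is only silent. Section 2.1 still requires that comparison, and a detailed analysis plan is announced.

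**Conclusion.** The point holds. As fixed in section 4.1, a significant result on endpoints 7–12 cannot be attributed to the app, because no control separates retention from common change. The size depends wholly on a drift that the protocol does not give. With no lasting effect and 34 participants, assumed drifts of 2 to 5 points produce significance in about 21% to 81% of trials at SD of change 10, and 13% to 52% at SD 14.1. These are illustrations, not an estimate of this trial's error rate. The primary endpoint and its sample size are not affected.

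**What to change.** First reconcile the post-app windows in the section 2.1 note with sections 2.2 and 3.3. The steps below presuppose the section 2.2 calendar. Then, in section 4.1 and the analysis plan:

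- (a) Add as the controlled retention analysis a baseline-adjusted GLM comparing the intervention group in weeks 4–6 with the control group in weeks 1–3. State that it is not concurrent and that its SE is about 3.4 points against 1.7 for the pooled change (17 per group, SD 10).
- (b) Report the control group's weeks 1–3 against baseline as the drift estimate.
- (c) Report the weeks 4–6 group contrast only as the effect of stopping, and state that non-significance is not evidence of sustained benefit.
- (d) Keep the pooled change as an uncontrolled, descriptive result.
- (e) Align the comparators: section 2.1 names the on-app period, section 4.1 does not.

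If a mixed model with app state and period is also wanted, present it as a separate estimator with SE about 4.9 to 6.3 and its equal-effect assumption stated.

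The cost is wording and one extra main model, on closed-loop data already collected from both groups at Visits 1 and 2. The price is a wider interval: a lasting effect of 5 points would be detected in only about 29% of trials.

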#### **Primary endpoint:**

*The primary objective will be addressed by evaluating the following endpoint:*

- 1) Percentage of time with sensor glucose in the target range (3.9 to 10.0mmol/L, %)

Note: Time in target range will be calculated over the complete 3-week intervention period (Day 1 to Day 21).

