#### **Pre-defined exploratory endpoints:**

*The following endpoints will be examined to assess various aspects of SNAQ app use in terms of usefulness, nutrition literacy, psychosocial, and behavioral impact. Pre-specified exploratory endpoints will be reported as point estimates with 95% confidence intervals (unadjusted for multiple testing), so definite inferences cannot be made regarding those endpoints.*

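### The flat 5% significance rule covers all eleven secondary endpoints with no testing order or adjustment, while the multiplicity caveat is confined to the exploratory endpoints

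*Protocol*

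**What the plan says.** Section 2.1 of the protocol names one primary endpoint, time in target range over the three-week intervention period, and eleven numbered secondary endpoints. Numbers 2 to 6 concern efficacy: time above and below range overall, and time in, above and below range after main meals. Numbers 7 to 12 concern sustainability: changes in the same six measures once the app is stopped.

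Section 4.1 (Statistical analysis) says that the efficacy endpoints are compared between groups with baseline adjustment, and that sustainability is analysed as a paired comparison pooled over both groups. It then states: "P-values below 5% will be considered statistically significant". It gives no order of testing, no gate behind the primary endpoint and no adjustment.

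The next sentence of section 4.1 limits inference for the exploratory endpoints only. Section 2.1 says the same at the head of the exploratory list: "Pre-specified exploratory endpoints will be reported as point estimates with 95% confidence intervals (unadjusted for multiple testing), so definite inferences cannot be made". No such limit is attached to endpoints 2 to 12. Section 4.1 also announces a detailed SAP, to be written before the study starts; it is not available here.

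**The concern.** The protocol gives the lack of multiplicity adjustment as its reason for withholding firm conclusions from the exploratory endpoints. It provides no adjustment for the secondary endpoints either, yet attaches no warning to them. Read together, the two sentences place the secondary endpoints on the side where a p-value below 5% counts as a finding.

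The overlap between endpoints makes this more awkward. Times in, above and below range sum to 100%, both overall (endpoints 1 to 3) and after meals (4 to 6), and the corresponding changes (7 to 9 and 10 to 12) sum to zero. One shift in glucose can therefore appear as several significant results that look like separate confirmations.

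What is at stake is the standing of secondary claims in the report. The primary conclusion is not at risk.

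**Working it through.** **1. The plan's own figure, to establish what is not affected.** The protocol states no familywise error rate. Its one design figure concerns the primary endpoint. The inputs, from section 4.1, are a 10-point difference ("Assuming a mean improvement of 10% in the intervention group with no change in the control group"), "a within-participant standard deviation of 10% in both groups", two-sided alpha 5% and power 80%.
- Normal approximation: n per group = 2 × (1.960 + 0.842)² × (10/10)² = 15.7, so 16.
- Two-sample t-test: n = 16.7, so 17 per group and 34 in total, as stated; power at 17 per group is 80.7%.
- Drop-out: 17 / 0.8 = 21.25, so 22 per group and 44 in total, as stated.

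The primary endpoint is a single test at two-sided 5%. Nothing below changes that test or these numbers.

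**2. Number of secondary tests.** Endpoints 2 to 12 make 11: five on efficacy (2 to 6) and six on sustainability (7 to 12).

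**3. Ceiling under independence.** With k tests each at 5% and every null hypothesis true, P(at least one false positive) = 1 − 0.95^k. For two-sided tests on jointly normal statistics, independence gives the largest value, so these are upper limits.

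| Set of endpoints | k | 1 − 0.95^k | Expected false positives (0.05 × k) |
|---|---|---|---|
| Efficacy, 2 to 6 | 5 | 22.6% | 0.25 |
| Sustainability, 7 to 12 | 6 | 26.5% | 0.30 |
| All secondary | 11 | 43.1% | 0.55 |

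**4. Allowing for correlation.** The ceiling cannot be reached here, because the ranges are tied by their fixed sum and postprandial time is part of total time. The protocol gives no correlations, so equal correlations between test statistics were assumed and simulated (400,000 replicates) in two ways: efficacy and sustainability as two mutually independent blocks, and all eleven as one block.

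| Assumed correlation | Five efficacy | Six sustainability | Eleven, two blocks | Eleven, one block |
|---|---|---|---|---|
| 0.3 | 20.9% | 24.0% | 39.9% | 37.5% |
| 0.5 | 18.3% | 20.7% | 35.1% | 30.5% |
| 0.7 | 14.9% | 16.5% | 28.9% | 22.3% |
| 0.9 | 10.2% | 10.9% | 19.9% | 13.2% |

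Over this range the eleven-test rate runs from about 13% to about 40%. It would fall to 5% only if all the tests were perfectly correlated.

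**The case against.** The strongest reply is that ordering or adjusting secondary endpoints is normally SAP work, and a SAP is promised before the study starts. The sentence on p-values sets a threshold. It does not say that the p-values are unadjusted, that the secondary endpoints are confirmatory, or that they may be claimed if the primary endpoint fails. A fixed-sequence procedure tests each step at 5%, so a SAP could add one without contradicting the protocol. Many trials with one alpha-controlled primary endpoint also treat secondary endpoints as supportive without formal adjustment.

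Much of this stands. The unadjusted reading follows from an unrestricted rule and is not spelled out, and the SAP may yet repair it. Had the protocol merely been silent, there would be no point to raise. But it states a significance rule without limit and then confines its multiplicity caveat to one tier. If the secondary endpoints are meant to be supportive, the text does not say so, and its contrast with the exploratory tier suggests otherwise.

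The objection that the eleven endpoints are not one family also has force. Endpoints 2 to 6 rest on a randomized comparison, while 7 to 12 rest on a pooled before-and-after comparison serving a separate objective. That is why the two sets are shown separately; each has its own ceiling above 20%.

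**Conclusion.** The point holds as a defect in a stated rule: followed as written, section 4.1 lets any of endpoints 2 to 12 be called significant at an unadjusted 5%, whatever the primary result. The chance of at least one false-positive secondary result is at most 22.6% (efficacy), 26.5% (sustainability) or 43.1% (all eleven). With correlation it is lower but still above 5%, at about 13% to 40% for eleven tests. These figures assume that all the null hypotheses are true, that the test statistics are jointly normal, and that the correlations are equal and between 0.3 and 0.9; the correlations are assumptions, not protocol figures.

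Four stronger readings are not supported:
- A reader might take 43% as the expected error rate. It is a ceiling that these endpoints cannot reach.
- A reader might infer that the primary endpoint is underpowered and so likely to give way to a secondary one. On the protocol's stated assumptions its power is 80.7%; any dispute over those assumptions is a separate matter.
- A reader might infer that a chance secondary result is likely to become the trial's conclusion. The protocol ties its one hypothesis, its primary objective and its sample size to time in range, and even the ceiling is below one half.
- A reader might count two tests for each sustainability endpoint, because the note in section 2.1 mentions both baseline and the app period. That would make 17 tests and a ceiling of 1 − 0.95^17 = 58.2%. The analysis text in section 4.1 names only the baseline comparison, so the count of 11 is used here.

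**What to change.** In section 4.1, state that the 5% significance rule applies to the primary endpoint. State also that endpoints 2 to 12 are supportive and will be reported as estimates with unadjusted 95% confidence intervals, under the same caveat as the exploratory endpoints. Allow one exception: a hierarchy that the SAP specifies before the study starts and that begins only after a significant primary result. If such a hierarchy is wanted, the trial team should choose and justify its order, since the protocol gives no basis for one.

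This takes one sentence, or two with the exception. It needs no extra participants, visits or data, and leaves the primary test and the 34/44 sample size unchanged. The cost is fewer nominally significant secondary claims, and a less sharp distinction in inference between the secondary and exploratory tiers unless the SAP adds the hierarchy.
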